#### Surgical severity

We redefined the surgical severity variable into three categories (moderate, major or complex major) depending on the type of procedure used to excise the tumor or to palliate symptoms.

The moderate severity category referred to transanal endoscopic microsurgery (TEM) or discharge colostomy; the major severity category to surgical techniques such as right/left hemicolectomy, any colectomy, total proctocolectomy, sigmoidectomy or transanal resection; and the complex major severity category corresponded to anterior resections or abdominoperineal amputation. Any intervention that involved a surgical colorectal technique, in addition to another procedure that affected any other organ, was considered a complex major surgical intervention.

We did not consider any colorectal cancer surgeries as belonging to the minor severity category.

#### pTNM staging

TNM classification was assessed according to the American Joint Committee on Cancer (AJCC), 7th Edition 2010 [14], and focused on the pre-intervention/clinical (cTNM) and the histopathological report (pTNM). For the final stage grouping, pTNM was considered. When only partial pTNM was available, a combination of cTNM and pTNM data were considered: (a) where the pM component was not recorded, pM was replaced by the corresponding cM stage or, when the latter was missing, pM was assumed to be pM0; (b) in subjects whose pN component was unobserved, the pTNM was classified as at least stage III if there was evidence that lymph nodes were infiltrated. Otherwise, pTNM was specified as stage II; and (c) tumors without pT value described pN0-pNx and pM0-pMx parameter values, where pTNM was therefore deemed to be stage II.

When pTNM was fully unobserved, it was replaced by the analogous cTNM data. If the latter information was also missing, it was recorded as a missing value.C.Statistical Analysis

In relation to the different study objectives, exploratory analysis of the population sample will be performed using mean and standard deviations for continuous variables (or median and interquartilic ranges, when the observed variables do not follow the normality distribution) and frequencies and percentages for qualitative variables.

Predictive models will be developed to address objectives 1 and 2. The overall sample will be randomly divided into derivation and validation sets. On the one hand, for binary outcomes (such as death, tumor recurrence, major complications, or readmission), multivariate hierarchical logistic models will be used. Goodness-of-fit of models will be assessed by means of the Hosmer–Lemeshow test (*p*-values > 0.05 indicate good model calibration) and the area under the Receiver Operating Curve (ROC), AUC, will be used to evaluate the discrimination ability of the final performance models. An AUC value > 0.80 will indicate that the model discriminates well. Furthermore, multivariate Cox regression models will be used to answer to those objectives. On the other hand, in cases of continuous outcomes (variables related to deterioration of quality of life) as with objective 3, the use of multivariate hierarchical linear mixed models is proposed. The intraclass correlation coefficient (ICC) will be calculated to assess the correlation among observations within a cluster by dividing the patient variance by the total sample variance. A small coefficient would indicate that patients and participant centers are independent.

For study endpoints related to health services research, the following statistical approaches will be used: for two-level outcomes, the Student’s t-distribution or the non-parametric Wilcoxon test (for non-normal distributions) will be applied. Where there are three or more categories in the outcome, ANOVA analysis or a Kruskal–Wallis approach (for non-normal distribution) are the proposed tests. Otherwise, for categorical variables, the Chi-square test (or Fisher’s Exact method, where required) will be used. Multivariate models will be used as needed for appropriate adjustments. For some analyses, subgroups based on tumor location (colon or rectum) will be identified.

An analysis of comparative costs between two alternative surgical approaches (open and laparoscopic surgery) will be performed. For this purpose, generalized linear models (GLM) will be employed using the patient level cost as the dependent variable and taking clinical covariates into account (age, sex, stage, among others). The statistical model will determine which covariates are associated with higher costs, as well as any significant differences in cost between the two alternatives. Analysis will be conducted at 2 and 5 years of follow up.

Finally, results related to treatment will be a valuable source of information for inclusion in a discrete-event simulation model reproducing a colorectal cancer-screening program. Clinical and quality of life data for treatment of colorectal cancer detected by screening or clinical approaches will be useful to assess not only the impact of screening, but also to compare different treatment strategies through a cost-effectiveness or budget impact analysis.

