#### Selection criteria

Patients will be deemed eligible for the study if they have undergone surgery for colorectal cancer in one of the participating hospitals. Colorectal cancer diagnosis is based on anatomopathological diagnosis after a biopsy by colonoscopy [10, 14, 15].

Inclusion criteria: diagnosis with colon cancer (up to 15 cm above the anal margin) and rectum (between the anal margin and 15 cm above it), where curative or palliative surgery by first time was applied. Exclusion criteria are colon or rectum in situ cancer, inoperable tumor, severe mental or physical condition which prevents the patient from responding to questionnaires, terminal illness, inability to respond to questionnaires for any reason, or lack of consent to participate in the study. Figure 2 illustrates a flow chart of the recruitment process. Recruitment data from participating hospitals as of December 2012 are provided in Table 1.

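### The staging rule lets a recorded pM0 stand over a recorded cM1 and leaves pMx undefined, so patients with metastases on pre-operative staging can be placed below stage IV

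*Protocol article*

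**What the plan says.** All of the staging rules stand in the protocol article under the heading on pTNM staging, within the section on missing data and recoding.

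- Basis of the final stage: "For the final stage grouping, pTNM was considered". The same paragraph ties pTNM to the pathology report and cTNM to the work-up before surgery.
- When clinical staging enters: "When only partial pTNM was available, a combination of cTNM and pTNM data were considered". If pTNM is wholly absent, cTNM takes its place.
- Rule (a), M component: "where the pM component was not recorded, pM was replaced by the corresponding cM stage or, when the latter was missing, pM was assumed to" (the default is M0).
- Rule (b), pN missing: "the pTNM was classified as at least stage III if there was evidence that lymph nodes were infiltrated". The alternative is "Otherwise, pTNM was specified as stage II".
- Rule (c), pT missing: "tumors without pT value described pN0-pNx and pM0-pMx parameter values, where pTNM was therefore deemed to be stage II".

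The selection criteria admit patients "where curative or palliative surgery by first time was applied", so metastatic patients belong to the cohort, and Table 2 reports 260 in stage IV. Clinical staging before surgery is collected (Data collection), and so are the pathology components (Data related to hospital admission). Stage is a named covariate of the cost model comparing open and laparoscopic surgery (Statistical Analysis).

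**The concern.** A bowel specimen carries no information about a distant lesion that was not sampled. A pM0 entry is therefore not, by itself, evidence against metastases seen on pre-operative staging. The article already accepts this in part: it trusts cM when pM is absent, and trusts the whole cTNM when pTNM is absent. It withdraws that trust once the pathology field holds pM0, without asking what the entry rests on.

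The result is that two patients with identical disease and identical pre-operative findings can receive different stages because one field was completed differently. At stake is the stage variable itself. Metastatic patients counted in lower stages would blur the contrast between stage IV and the rest, in the cost model and in any other model that adjusts for stage.

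**Working it through.** **1. Reproduce the figure that the rule feeds.** From Table 2, staged patients number 1581 + 892 + 260 = 2733, so 2749 − 2733 = 16 have no stage. Stage IV is 260/2733 = 9.51%, as printed. By location it is 60/766 = 7.83% (rectal) and 200/1967 = 10.17% (colon), also as printed. The table is internally consistent. It cannot show whether anyone was placed too low, because cM is not tabulated against pM.

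**2. Apply the rule to patients with cM1.** Each pM entry is tried with pMx read both ways.

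| pM entry | M used if pMx counts as recorded | M used if pMx counts as not recorded |
|---|---|---|
| pM1 | M1 | M1 |
| pM0 | M0, cM1 lost | M0, cM1 lost |
| pMx | Mx, cM1 lost | M1 |
| blank | M1 | M1 |

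The pM0 row loses the metastasis on either reading. The pMx row depends on the reading.

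**3. Worked cases, all with cM1.**
- pT3 pN1 pM0: pTNM is complete, cM is not consulted, stage III.
- pT3 pN1, pM blank: rule (a) brings in cM1, stage IV.
- pT3 pN0 pMx: stage IV if pMx means not recorded. If pMx is a recorded value handled like pM0, as in rule (c), stage II.

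With complete pT and pN and a recorded pM0, the patient could also land in stage 0 or I, so the misplacement is not confined to II and III.

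**4. Rules (b) and (c).** Rule (c) groups pMx with pM0 and assigns stage II without mentioning cM, but only when pT is missing. The fallback to stage II in rule (b) does not mention M at all. The text does not say that M is settled before either rule is applied.

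**5. Size, as a range.** The number of cM1 patients now below stage IV is not given. Assume a share f of the 1581 + 892 = 2473 patients in stages 0 to III. Patients moved = 2473f; corrected stage IV = 260 + 2473f; share of all stage IV placed too low = 2473f/(260 + 2473f).

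| f (assumed) | Patients moved | Stage IV after | % of 2733 | Share of stage IV placed too low |
|---|---|---|---|---|
| 0 | 0 | 260 | 9.51 | 0% |
| 0.25% | 6 | 266 | 9.74 | 2.3% |
| 1% | 25 | 285 | 10.42 | 8.7% |
| 2% | 49 | 309 | 11.32 | 16.0% |
| 5% | 124 | 384 | 14.04 | 32.2% |

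Because stage IV is small, a few dozen moves would change its make-up noticeably.

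**The case against.** The strongest reply has four parts.

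- **pM0 can be informative.** It may follow sampling of a suspected lesion that proved benign, and a hierarchy with pathology first is then right. This stands, and it rules out treating every pM0 as missing. It does not justify letting every pM0 override cM1 unexamined.
- **pMx may simply mean not recorded.** An x gives no M status, and rule (c) reaches only tumors lacking pT. This also stands. A reader might infer from "tumors without pT value described pN0-pNx and pM0-pMx parameter values" that pMx always blocks cM1, but the text does not go that far. What remains is an ambiguity on which two analysts could stage one patient differently.
- **No discordant record is shown.** Correct. A reader might infer that patients in this cohort have in fact been mis-staged. The article gives no such count, so only the possibility follows from the rule.
- **This is a condensed article.** The data-collection manual and the six-monthly checks may deal with discordant entries. That would excuse silence, but here a rule is printed and, as printed, it gives inconsistent results.

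A reader might also infer a definite bias in stage-specific mortality, contamination of analyses limited to stages I to III, or a pattern by hospital. The article gives no mortality by stage, describes no analysis limited to those stages, and says nothing about reporting habits by centre. Stage is named as a covariate only for the cost model; its use in the models for death and recurrence is likely but not stated.

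**Conclusion.** The point holds as a defect in the written rule. With cM1 recorded, pM0 leads to a stage below IV, while a blank pM with pT and pN recorded leads to stage IV. For pMx the outcome depends on a definition that the article does not give. The number of patients affected is unknown and may be zero; the range of 6 to 124 rests entirely on the assumed share of 0.25% to 5%. No effect on mortality estimates or odds ratios can be derived from the article. The correction is worth making because the components are already held and the result either repairs the stage variable or shows that it was sound.

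**What to change.** Replace rule (a) with a step that settles M before rules (b) and (c) are applied:

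1. M is M1 if either pM1 or cM1 is recorded, except where a pM0 reflects sampling of the suspected lesion or the record otherwise disproves cM1.
2. pMx is treated as not recorded and takes the cM value.
3. Any patient with M1 is stage IV, whatever is missing for pT or pN.

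Then re-derive stage from the stored cTNM and pTNM components, report how many patients move and from which stage, and use the re-derived stage in the cost model and in any other model that includes stage.

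The cost is a short change of text and a re-run of the derivation, plus a chart check of each discordant cM1/pM0 record. That check is real work, since the article lists no field stating what a pM0 entry was based on, but it is limited to the discordant records.

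### The staging rules set stage II whenever pN is unobserved without nodal evidence, whatever pT or M is recorded, and treat this and two related fills as observed data

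*Protocol article*

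**What the plan says.** The section on pTNM staging in the Protocol article adopts the AJCC 7th edition and uses pathological stage for the final grouping. For incomplete records it opens with a general principle: "When only partial pTNM was available, a combination of cTNM and pTNM data were considered". Three lettered rules follow.

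- Rule (a), pM not recorded: "pM was replaced by the corresponding cM stage or, when the latter was missing, pM was assumed to be pM0".
- Rule (b), pN not observed: the patient is placed in stage III or higher "if there was evidence that lymph nodes were infiltrated. Otherwise, pTNM was specified as stage II".
- Rule (c), pT not observed: "tumors without pT value described pN0-pNx and pM0-pMx parameter values, where pTNM was therefore deemed to be stage II".

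A separate paragraph covers a wholly unobserved pTNM. It is replaced by cTNM, and stage is left missing only if cTNM is missing too.

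Elsewhere, the section on statistical analysis lists stage among the covariates of the cost GLM comparing open and laparoscopic surgery. The covariates of the prediction models are not listed. Table 2 reports pTNM in three groups: 0/I/II, III and IV.

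**The concern.** Rule (b) decides stage from nodal evidence alone. It can therefore contradict components that were recorded, and it turns absence of evidence about nodes into node-negative disease. Rule (c) picks one stage when T is unknown and does not call on cT, although the general principle and rule (a) both use clinical data to fill pathological gaps. Rule (a) ends in an assumption of M0.

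Each fill is a single fixed value, and no distinction from observed stage is described for the analysis. Two things are at stake. Misclassified stage would bias the stage coefficient, and would leave residual confounding by stage in the adjusted open-versus-laparoscopic cost comparison. The uncertainty of the filled values is also ignored, so standard errors tend to be too small.

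The affected patients are unlikely to be a random subset. Palliative surgery is eligible, and the moderate severity class consists of "transanal endoscopic microsurgery (TEM) or discharge colostomy". Local excision in particular may leave nodes unexamined, so errors in stage could follow the type of procedure.

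**Working it through.** **Step 1. Reproduce Table 2.** Staged patients: 1581 + 892 + 260 = 2733. Shares: 1581/2733 = 57.85%, 892/2733 = 32.64%, 260/2733 = 9.51%. All three match the table. Without a stage: 2749 − 2733 = 16 (0.58%), made up of 770 − 766 = 4 rectal and 1979 − 1967 = 12 colon patients. For comparison, ASA class is missing in 2749 − 2673 = 76 (2.8%). I assume that Table 2 shows the variable after the rules were applied; the article does not say so outright. Either way, the table does not show how many patients each rule staged.

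**Step 2. Run typical records through the rules.** The comparison is the usual TNM grouping: any M1 is IV; otherwise positive nodes are III; otherwise T1-T2 is I and T3-T4 is II.

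1. pT1-T2, pN unobserved, no nodal evidence, M0. Rule (b) gives II. If the nodes are taken as negative, as the rule does, the grouping gives I.
2. pN unobserved, no nodal evidence, M1 recorded. The literal wording of (b) gives II; the grouping gives IV. The first arm of (b) says stage III or above, which leaves room for IV. The second arm has no such allowance.
3. pT3-T4, pN unobserved, nodes not examined, M0. Rule (b) gives II. The true stage is II or III and is unknown.
4. No pathology at all, cT1 cN0 cM0. The fully-unobserved rule gives I through cTNM. Now add a recorded pN0, still with no pT. Rule (c) gives II. An extra observation consistent with stage I has moved the patient to II.
5. No pT, pNx, pMx. Rule (c) gives II. If x means not assessed, nothing is observed from pathology, and the fully-unobserved rule gives cTNM or missing. The two rules can disagree on the same patient.
6. No pT, pMx, cM1. Rule (a) would supply M1. Rule (c) still lists pMx among the records it sends to II. Which rule acts first is not stated.
7. pM and cM both missing. Rule (a): "when the latter was missing, pM was assumed to be pM0". No uncertainty is carried forward.

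Records 1 and 4 can move patients up, records 2, 3, 6 and 7 can move them down, and record 5 can go either way. The net direction is therefore not determined.

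**Step 3. What the size could be, under assumptions.** The number filled is not given. Purely for illustration, suppose that 1% to 10% of the 2733 staged patients were set to II by default, and that 10% to 42% of those were truly III or IV. The upper value is the tabulated share, (892 + 260)/2733 = 1152/2733 = 42.15%.

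- Low end: 0.01 × 2733 × 0.10 ≈ 3 patients. That is 2.7/1581 = 0.2% of the 0/I/II group and 2.7/(1152 + 2.7) = 0.2% of true III/IV patients.
- High end: 0.10 × 2733 × 0.4215 ≈ 115 patients. That is 115/1581 = 7.3% of the 0/I/II group and 115/(1152 + 115) = 9.1% of true III/IV patients.

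Both ranges are assumed, so this shows only that the effect could be trivial or noticeable. I-versus-II errors do not appear here, because Table 2 pools stages 0, I and II.

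**The case against.** The best defence is context. The lettered rules sit under the principle of combining clinical and pathological data within AJCC grouping, and M is dealt with first, in (a). The nodal evidence in (b) may include cN. A condensed sentence need not reveal the real coding, and counts, flags and sensitivity analyses are usually left to a fuller document.

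Much of this limits the point. A reader might infer several stronger things that the article does not support:

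- *That patients with recorded M1 were in fact coded stage II.* This follows only from the literal wording; the article does not show that it was done.
- *That rule (c) overrides recorded spread.* It is confined to pN0-pNx and pM0-pMx, so no recorded M1 or positive node is overridden. For N0 M0, stage II is an unsupported choice among 0, I and II, not a certain error.
- *That every fill goes to a favourable stage.* For an early pT, stage II is the worse one.
- *That 892/(892 + 1581) = 36% of defaulted patients are understaged.* Rule (b) has already removed those with nodal evidence, and the share cannot apply to patients with recorded pN0.
- *That palliative diversion without a specimen defaults to II.* It would more naturally count as fully unobserved and go to cTNM or to missing.
- *That missingness is concealed.* The rules are published, and stage with no data at all stays missing.
- *That stage is a declared covariate of the survival and recurrence models.* It is named only for the cost GLM; its use elsewhere is plausible but inferred.

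What the defence does not answer is the wording of (b) on pT. Nothing in the context sends a recorded pT1-T2 to stage I. Nor does it answer the unused cT in (c) or the disagreement in record 5. These are features of rules that the article states and fixes, not details it omits.

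**Conclusion.** The concern holds in a limited form. As written, rule (b) ignores recorded pT and does not protect a recorded M1, and it takes unexamined nodes as negative. Rule (c) fixes stage II without cT and can conflict with the rule for a wholly unobserved pTNM. Rule (a) falls back on M0. All are single deterministic fills in a variable used for adjustment in the cost model and plausibly in the prediction models.

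The number of patients affected, and the size and direction of any bias, cannot be determined from the article. The conclusion rests on reading the rules as worded and on the usual TNM grouping; it does not rest on the illustrative range. The rules should be corrected because the change is specific and cheap and uses data already collected. There is no evidence that the study's results are seriously distorted.

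**What to change.** - Derive stage from recorded components in a stated order: any pM1 or cM1 first, then nodes, then T.
- Fill missing pT and pN from cT and cN, as rule (a) already does for M with cM. Say whether the nodal evidence in rule (b) includes cN.
- Say what pNx and pMx mean, so that rule (c) and the fully-unobserved rule cannot both apply to one record.
- Treat what is still unknown as missing and multiply impute it, using the recorded components, procedure, tumour site, tumour markers and outcome, instead of fixing it at stage II or M0.
- Flag derived stages, report how many patients each rule staged, and repeat the models that use stage without those patients.

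The cost is some recoding of collected variables, a routine imputation and slightly wider intervals. No new data are needed.

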**Methods:**

Design: a prospective multicenter cohort study with a follow up period of up to 5 years after surgical intervention. Participant centers: 22 hospitals representing six autonomous communities of Spain. Participants/Study population: Patients diagnosed with colorectal cancer that have undergone surgical intervention and have consented to participate in the study between June 2010 and December 2012. Variables collected include pre-intervention background, sociodemographic parameters, hospital admission records, biological and clinical parameters, treatment information, and outcomes up to 5 years after surgical intervention. Patients completed the following questionnaires prior to surgery and in the follow up period: EuroQol-5D, EORTC QLQ-C30 (The European Organization for Research and Treatment of Cancer quality of life questionnaire) and QLQ-CR29 (module for colorectal cancer), the Duke Functional Social Support Questionnaire, the Hospital Anxiety and Depression Scale, and the Barthel Index. The main endpoints of the study are mortality, tumor recurrence, major complications, readmissions, and changes in health-related quality of life at 30 days and at 1, 2, 3 and 5 years after surgical intervention.

Statistical analysis: In relation to the different endpoints, predictive models will be used by means of multivariate logistic models, Cox or linear mixed-effects regression models. Simulation models for the prediction of discrete events in the long term will also be used, and an economic evaluation of different treatment strategies will be performed through the use of generalized linear models.

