## Methods/design

### Study design

An observational analytic prospective cohort study with a planned patient follow up period of 5 years following surgical intervention.

Setting: patients recruited from 22 hospitals representing 9 provinces in Spain, all of which operate under the Spanish National Health Service (SNHS), which is responsible for the majority of the national population. All applicable residents have free access to their primary care physician and to the hospital ED. Participating hospitals are: Hospital de Antequera, Hospital Costa del Sol, Hospital Universitario de Valme, Hospital Universitario Virgen del Rocío, Hospital Universitario Virgen de las Nieves, Hospital Universitario de Canarias, Corporació Sanitaria Parc Taulí, Althaia, Hospital del Mar, Hospital Clínico San Carlos, Hospital Universitario La Paz, Hospital Infanta Sofía, Hospital Universitario Fundación Alcorcón, Hospital Galdakao-Usansolo, Hospital Universitario Araba, Hospital Universitario Basurto, Hospital Universitario Cruces, Hospital Hospitalario Donostia, Hospital Bidasoa, Hospital de Mendaro, Hospital de Zumarraga and Hospital Universitario Doctor Peset.

Research population: Patients diagnosed with colorectal cancer that underwent surgical intervention at one of the listed hospitals between June 2010 and December 2012. Patients were informed of the study objectives and invited to voluntarily participate. Patients were included in the study sequentially.

Expected duration of the study: patients will be followed until 5 years after the surgical index intervention, or until death.

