### Follow-up

Follow-up visits up to two years will be performed at all 22 participating hospitals. Due to financial restrictions and organizational resources, 3- and 5-year follow-up visits will be restricted to 18 hospitals (Hospital de Antequera, Hospital Costa del Sol, Hospital Universitario de Valme, Hospital Universitario Virgen del Rocío, Hospital Universitario Virgen de las Nieves, Hospital Universitario de Canarias, Corporació Sanitaria Parc Taulí, Hospital del Mar, Hospital Clínico San Carlos, Hospital Universitario La Paz, Hospital Infanta Sofía, Hospital Universitario Fundación Alcorcón, Hospital Galdakao-Usansolo, Hospital Universitario Araba, Hospital Universitario Basurto, Hospital Universitario Cruces, Hospital Hospitalario Donostia, and Hospital Universitario Doctor Peset).

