### Data management and statistical analysis

A.Sample size selection

Studies of predictive model development indicate that is necessary to include at least 10 events of the dependent variable of interest (in this case: mortality, major complications, relapses or readmissions) for each independent variable included in the multivariate logistic regression model [31, 32]. Therefore, we estimated that at least 100 events of the dependent variable in the sample are required in order to ensure that the regression model would adequately converge. Previous data indicate that the number of events of the dependent variable mortality would be > 15 % of patients operated on in the first year, higher that the expected percentages of other parameters. We therefore estimated that more than 300 events of any of the dependent variables of interest should be included.

Sampling: we consecutively collected all new cases until the sample size was achieved.B.Missing data assumptions and recoding of variables

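### Recurrence, complications and readmission beyond 30 days are to be modelled by logistic and Cox regression without treating death as a competing event

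*Protocol article*

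**What the plan says.** The Statistical Analysis part of the protocol article fixes the model families. It says that "for binary outcomes (such as death, tumor recurrence, major complications, or readmission), multivariate hierarchical logistic models will be used", and then: "Furthermore, multivariate Cox regression models will be used to answer to those objectives". For continuous outcomes, described as "variables related to deterioration of quality of life", "the use of multivariate hierarchical linear mixed models is proposed".

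Four other places bear on the point:

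- **Horizon.** The Abstract lists mortality, recurrence, major complications, readmissions and "changes in health-related quality of life at 30 days and at 1, 2, 3 and 5 years after surgical intervention" as main endpoints. Under Study design, "patients will be followed until 5 years after the surgical index intervention, or until death".
- **Frequency of death.** The sample-size text expects that the "dependent variable mortality would be > 15 % of patients operated on in the first year", and says that this is above what is expected for the other outcomes.
- **Late visits.** Under Follow-up, "3- and 5-year follow-up visits will be restricted to 18 hospitals".
- **Missing complications.** The Complications paragraph records missing items as no complication, at measurement points up to 5 years. It makes no exception for patients who have died or are no longer followed.

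The article nowhere mentions competing risks, cumulative incidence, cause-specific hazards, or what a quality-of-life score means after death. Anticipated issues discusses loss to follow-up and missing questionnaires, but not death.

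**The concern.** By the plan's own forecast, death is more frequent than any of the non-fatal outcomes that it can prevent from being observed. The Expected outcomes section wants risk factors, bedside prediction rules and a medium-term prognosis for patients. Each planned model answers a different question once death intervenes:

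- **Logistic, dead coded event-free.** The odds ratio reflects both the effect on the event and the effect on dying first. A factor that only raises mortality will appear to lower recurrence or readmission.
- **Logistic, patients not followed to the horizon.** Such a model cannot use partial follow-up. These patients are dropped, or counted as event-free without having been observed.
- **Cox, censored at death.** The hazard ratios are sound, but one minus the resulting survival curve is the risk in a population where nobody dies first.
- **Linear mixed model.** A likelihood-based fit implicitly continues trajectories past death unless the target is defined as change while alive.

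At stake are which factors are named as risk factors and whether the absolute risks given to patients are right.

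**Working it through.** **1. The plan's own figures.** 10 events × 10 predictors = 100 events, though the article does not state the number of predictors. With 15% first-year mortality, 0.15 × 2749 = 412 deaths. That agrees with the stated more than 300 events as a lower bound (300 / 0.15 = 2000 patients). No target sample size is stated, so 300 cannot be derived exactly. About 412 patients would therefore be dead by 1 year and no longer at risk of later events.

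**2. Patients without late visits.** Comparing the 18 hospitals under Follow-up with Table 1 leaves Althaia 100, Bidasoa 33, Mendaro 28 and Zumarraga 39. The sum is 200, and 200 / 2749 = 7.3%. This is an upper bound, because some will have died by year 2. Read literally, the missing-complication rule records those still alive as complication-free at 3 and 5 years.

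**3. Absolute risk with deaths censored.** The article gives no recurrence rate and no mortality after year 1, so the hazards are assumptions: recurrence λ = 0.06 per year, and death without recurrence μ = 0.03, 0.05 or 0.10 per year.

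- Deaths censored: 1 − exp(−λt)
- Cumulative incidence: λ/(λ+μ) × [1 − exp(−(λ+μ)t)]

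| Horizon | Deaths censored | Cumulative incidence, μ = 0.03 / 0.05 / 0.10 | Ratio |
|---|---|---|---|
| 2 years | 11.3% | 11.0% / 10.8% / 10.3% | 1.030 / 1.050 / 1.101 |
| 5 years | 25.9% | 24.2% / 23.1% / 20.7% | 1.073 / 1.123 / 1.255 |

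For example, at 5 years with μ = 0.10: 0.06/0.16 × (1 − exp(−0.8)) = 0.375 × 0.551 = 0.207.

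**4. The same check using the article's 15%.** Take 15% death in year 1, then assume 0 to 15% per year later and event rates of 5 to 12% per year. For an 8% event rate in year 1, λ = −ln 0.92 = 0.083 and μ = −ln 0.85 = 0.163. Cumulative incidence is 0.083/0.246 × (1 − 0.92 × 0.85) = 7.4%, against 8.0% with deaths censored, a ratio of 1.08. Over the whole grid the ratio is 1.08 at 1 year, 1.12 to 1.17 at 2 years and 1.15 to 1.44 at 5 years. With 8% events and 10% later mortality, the 5-year risks are 34.1% and 25.7%. This grid lies towards the high side, because the 15% is all-cause and includes deaths after the event, which do not compete with it.

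**5. Odds ratios.** Take the hazards of step 3 and a factor that doubles μ but leaves λ unchanged. With μ going from 0.10 to 0.20, 5-year incidence falls from 20.7% to 0.06/0.26 × (1 − exp(−1.3)) = 16.8%, an odds ratio of 0.78. For μ starting at 0.03 and 0.05, the odds ratios are 0.91 and 0.87. The true effect on the event hazard is null in all three cases.

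**The case against.** The case against has several parts, and much of it stands.

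- **Fixed-horizon coding is not wrong in itself.** A reader might infer that counting a patient who died without recurrence as having no recurrence gives a false risk. With complete follow-up to the horizon, that coding targets the real cumulative incidence. What remains is how the odds ratio is read and what happens to incompletely followed patients.
- **Fine-Gray shows the same apparent protection.** In step 5, the ratios on the complementary log-log scale are 0.92, 0.88 and 0.79, close to the logistic 0.91, 0.87 and 0.78. This is a reason to take risk factors from cause-specific models. It is not a defect peculiar to logistic regression.
- **The Cox model may already be cause-specific.** The article says only multivariate Cox regression. Censored at death, its hazard ratios are valid. The article nowhere says that absolute risks will be computed from it, and it attaches calibration and AUC to the logistic models.
- **The effect is small early.** The Background gives 1 or 2 years as examples of medium-term. On the hazards of step 3, the 2-year excess is at most about one percentage point.
- **The four hospitals are an administrative matter.** Restricting late analyses to the other 2549 patients would be defensible. The article does not state that restriction, and its missing-complication rule points the other way.
- **Detail may sit in an analysis plan.** Censoring rules often do. But this article chooses the models, sets a coding rule, forecasts death as the most frequent outcome, and offers itself as the reference for later papers.

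For quality of life, a reader might infer that decline will be understated because the sickest patients die. The documents do not establish a direction. They only leave the target undefined after death.

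**Conclusion.** The point holds in a limited form. For non-fatal outcomes beyond 30 days, the plan does not treat death as a competing event although it expects death to be common. Logistic odds ratios will mix two effects, and incompletely followed patients cannot be handled properly at a fixed horizon. Any absolute risk taken from Cox regression censored at death will be too high: about 3-10% relative at 2 years and 7-25% at 5 years under the assumed constant hazards of step 3. These sizes depend on assumed rates, and the effect at 30 days is small.

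The documents do not support saying that the planned logistic or Cox models are invalid, that inflated risks will certainly be published, or that the 15% is wholly a competing rate. The objectives might also be read as composites including death, which would remove the problem for those endpoints, but the analysis text lists the outcomes separately. The change should be made before the 1- to 5-year models are fitted. It does not undermine the cohort or its 30-day analyses.

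**What to change.** 1. Keep logistic models for 30-day outcomes.
2. For later recurrence, complications and readmission, use cause-specific Cox models for risk factors. For predicted risk, use cumulative incidence (Fine-Gray or combined cause-specific models), with discrimination and calibration assessed on that same scale. This applies where event times are available.
3. Where only a yes/no per visit exists, use fixed-horizon models with death as its own outcome category.
4. In time-to-event analyses, censor losses at last contact and the four hospitals at 2 years.
5. Do not apply the missing-means-no-complication rule to patients who have died or are no longer followed.
6. For quality of life, state that change is estimated while alive and report it beside the proportion dead at each visit. A joint longitudinal-survival model can be an optional sensitivity analysis.

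The cost is a few sentences of analysis text, standard software and slightly more complex analysis and reporting. The article does not say outright that event dates are recorded. The planned Cox models imply it, but complications are described as yes/no at each measurement point, so item 3 may be the workable route for them.
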